### 2.4 Procedure

Before the experiment, the demographic data of all subjects will be first collected. We then explained the experimental process, test actions, and precautions to the participants. Adequate time will be provided for them to acclimate to the experimental process, ensuring a comprehensive understanding of the experimental requirements. Subsequently, fNIRS equipment and sEMG sensors will be affixed to each participant.

The experimental protocol consists of three distinct motor tasks: level walking, ascending stairs, and descending stairs. Participants will perform three tasks in a random order, with each task being repeated three times. There will be a 5 min interval between tests to allow participants to rest adequately and ensure that the fNIRS spectral signals of each test return to the baseline. Tests will be conducted on the KOA patients first, followed by the healthy controls. During the level walking, the patients will be instructed to walk at a normal, comfortable self-selected speed (SSS) for 30 s each time, with SSS defined as the average velocity from three timed baseline walks. The stair program evaluation will use standardized stairs under the same SSS conditions, maintaining consistent handrail non-use protocol across groups. The staircase consisted of 10 steps, with each step having a height of 12 cm, conforming to the standard specification for steps in China. To mitigate speed-related confounding effects, healthy controls will be pace-matched to the patient cohort’s average speed under the same conditions. A schematic overview of the experimental protocol is depicted in Figure 2. During the test, if the participant experiences any discomfort (e.g., dizziness, or falls), the testing will be immediately stopped and undergo medical evaluation of whether to continue.

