### 2.3 Participants

The study will be conducted in the Department of Rehabilitation at Shanghai Seventh People’s Hospital from August to September 2025. KOA patients will be recruited from the hospital’s outpatient clinics or nearby community health centers through posters displayed by doctors or therapists. Participants who express their interest in the study will be evaluated for eligibility to determine whether they meet the inclusion criteria for this research. At the same time, researchers will obtain consent in accordance with the principle of informed consent to confirm the voluntariness of the participants. The inclusion criteria: (1) age from 50 to 75 years; (2) KOA diagnosis following the American College of Rheumatology’s clinical criteria; (3) clinical and radiological signs in the right knee only; (4) Kellgren-Lawrence grade II or III; (4) chronic pain (present for no less than 3 months) exceeds 30 out of 100. The exclusion criteria: (1) a history of severe knee injury or rheumatic disorders; (2) a history of cerebrovascular disease, mental illness or brain metal implantation; (3) drug/alcohol abuse; (4) cognitive impairment or failure to cooperate. HC will be recruited from communities around the hospital via word-of-mouth and advertisements, who have no history of diseases affecting joints and brain. All individuals need to have a right lower limb dominance, determined by their kicking preference (Willems and Ponte, 2012). Before the study is carried out, all subjects are required to complete a written informed consent form in accordance with ethical review requirements.

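### Patients are tested before controls, and controls walk at the patients' average speed, so the group main effect cannot be separated from test period or imposed pace

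*Protocol article*

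**What the plan says.** All the relevant design choices stand in section 2.4 (Procedure) of the protocol article.

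- **Order of the groups:** "Tests will be conducted on the KOA patients first, followed by the healthy controls".
- **Patients' speed:** "the patients will be instructed to walk at a normal, comfortable self-selected speed (SSS) for 30 s each time". This speed is defined as the mean of three timed baseline walks.
- **Stairs:** "The stair program evaluation will use standardized stairs under the same SSS conditions".
- **Controls' speed:** "healthy controls will be pace-matched to the patient cohort’s average speed under the same conditions". The stated purpose is to limit confounding by speed.
- **Randomisation:** it applies only within a participant: "Participants will perform three tasks in a random order, with each task being repeated three times".

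Section 2.3 places the study at one site, "from August to September 2025". Section 2.8 models brain activation by group, task and their interaction, and muscle activation by group and task. It states no term for period or speed. The limitations in section 3 concede that speed differences may remain despite pacing, and leave speed as a covariate to future work. They mention neither the order of testing nor the fact that controls walk at a speed that is not their own.

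**The concern.** The KOA-versus-control comparison is a stated aim of the design (section 2.1). With patients tested first and controls afterwards, whatever changes over the study falls between the groups: operator practice in fitting the cap, adjustment of the optode spacing between 25 and 35 mm, or the state of the equipment. Holding a given speed may also place its own demand on the sensorimotor areas that the study measures, and the text describes that demand for controls only.

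Matching to one average has a further weakness. It equates the mean speed but not the spread: patients keep their range of speeds, while controls have almost none.

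At stake is the reading of a group main effect, whether in the cortical regions or in the sEMG indices. Such a difference could come from KOA, from test period, from imposed pace, or from any mixture of these. The repair has to be made in the design, before testing.

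**Working it through.** **1. Can the effects be separated?** Code each of the 40 participants (20 per group, section 2.2) with an intercept, group (KOA 0, control 1), period (first 0, second 1) and imposed speed (no 0, yes 1). Under section 2.4 as written, the last three columns are identical. The design matrix has 4 columns and rank 2, so a period or pacing term added to the section 2.8 models could not be estimated apart from group.

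**2. Which effects are touched?** Let a shift s enter every control measurement.
- Group main effect: the contrast of group means moves by s in full.
- Group-by-task interaction: (control − KOA) in task A minus (control − KOA) in task B moves by s − s = 0. A pacing effect that differs between level walking and stairs would not cancel.
- Correlations of activation with VAS and WOMAC: these are computed within KOA patients only, so a shift in controls does not enter.

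**3. The plan's own sample size, to fix the scale.** Section 2.2 gives effect size f = 0.40, alpha 0.05 and N = 36, raised to 40 for 10% dropout. For the between-group test of a repeated-measures ANOVA with 2 groups, m = 3 tasks and an assumed correlation ρ = 0.5:

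λ = f²·N·m / (1 + (m − 1)ρ) = 0.16 × 36 × 3 / 2 = 8.64, with 1 and 34 df.

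Power is 0.815, and 36 is the smallest even N that reaches 0.80; 36 / 0.9 = 40. The figure reproduces if the printed power of 0.20 is read as β. For two groups, f = 0.40 corresponds to a difference of 2f = 0.8 SD of a single measurement.

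**4. Illustration of size.** The document gives neither a drift nor a correlation, so both are assumptions. The SD of a participant's mean over 3 tasks, in units of the single-measurement SD, is √((1 + 2ρ)/3), which is √(2/3) = 0.816 at ρ = 0.5. With 20 per group and no true group difference, the t-test has 38 df and noncentrality (shift / 0.816) × √10.

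| Shift (SD of one measurement) | Noncentrality | False group effect, two-sided 0.05 |
|---|---|---|
| 0 | 0 | 5% |
| 0.2 | 0.77 | 11.7% |
| 0.3 | 1.16 | 20.5% |
| 0.5 | 1.94 | 47.1% |

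Sensitivity at a shift of 0.3 SD: 27% for ρ = 0.2, 21% for ρ = 0.5 and 17% for ρ = 0.8. With a Bonferroni level of 0.05/6 for the six regions and ρ = 0.5, the rate is about 6% per test, against a nominal 0.8%.

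**5. Does interleaving cure the period overlap?** Put half of each group in each half of the window. The matrix of intercept, group and period then has full rank, 3 of 3. The variance of the group contrast stays at 2/20 = 0.10 σ², the same as without a period term, so no participants need be added. The pacing overlap remains unless both groups walk under the same pacing condition.

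**The case against.** Several points on the other side are sound.

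- **No cue is described.** The text says that controls are pace-matched and names no metronome or other device. A reader might infer that controls walk to a cue while patients walk freely. The document supports only an imposed speed for controls against a self-selected speed for patients. The limitations speak of standardised pacing without restricting it to controls, and the figure showing the procedure is not available.
- **The order is not forced.** A reader might infer that matching to a cohort average requires every patient to be finished first. It does not, because the timed baseline walks could supply the speeds beforehand. This weakens the case for the stated order: the sequence is a scheduling choice and can be changed.
- **Safeguards exist.** There is one site, one device and a two-month window. The protocol digitises the Cz position, maps channels to a standard space and checks optical coupling in real time. The outcome is a task-evoked coefficient from relative HbO changes, so an additive offset between sessions drops out, and sEMG is normalised to maximum voluntary contraction. These steps make drift from fitting or equipment less likely. They do not remove operator effects or the effect of walking at an imposed speed.
- **The reach is limited.** The article's specific objective, relating activation to pain and function, is analysed within patients and is not touched.
- **The percentages depend on assumptions.** They hold for one uncorrected test, whereas section 2.8 plans corrections. The rate per test falls under correction, but at 0.3 SD it still exceeds its nominal level.

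**Conclusion.** The point holds for the group main effect. As section 2.4 is written, group coincides with test period and with walking at an imposed speed, and no term added to the section 2.8 models could separate them. That conclusion rests on the design alone and needs no assumption about size.

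The size of any bias is unknown. The range of about 12% to 47% false group effects for shifts of 0.2 to 0.5 SD is an illustration. It assumes a correlation of 0.5, 20 per group and a single 0.05 test, and those shifts are 25% to 62.5% of the planned 0.8 SD (0.2/0.8 and 0.5/0.8). It does not predict what this study will show.

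A reader might go further and conclude that the study's results as a whole are uninterpretable. The document does not support that: a shift common to the three tasks cancels from the group-by-task interaction, and the within-KOA correlations are unaffected. The limitation already conceded, residual speed differences, covers neither the test order nor the imposed speed.

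**What to change.** In section 2.4, drop the patients-first order and interleave the two groups through the August to September window. Replace the cohort average by the recorded speeds, task by task, of one already tested patient for each control, frequency-matched on age and sex where feasible. This removes the period overlap and also matches the spread of speeds, which an average cannot do.

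Record actual speed in both groups, report test date by group, and add to the limitations that controls walk at an imposed speed, since interleaving does not remove that overlap.

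Two further steps are not required. Giving patients the same pacing condition at their own speed would make the groups alike in this respect, but it works against the aim of observing natural walking, so it is the sponsor's choice. Pair as a fixed blocking factor would cut the error df from 38 to 19. If four dropouts each broke a different pair, the 16 complete pairs would have power of about 0.74 with no within-pair correlation, against 0.81 for 18 per group unpaired (f = 0.40, ρ = 0.5).

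The cost is scheduling effort, a wording change and slightly less freedom in the order in which controls are recruited. The sample size stays at 40.

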**FIGURE 2 F2:**
[figure not shown]
Schematic overview of the experimental protocol.

### 2.5 fNIRS data acquisition and preprocessing

A portable multi-channel wireless fNIRS device (Brite24, Artinis Medical Systems, Netherlands) will be employed to capture cerebral fNIRS signals to evaluate alterations in brain activity patterns during movement. Following the international 10–20 system for electrode placement, the Cz electrode location of participants is identified using three-dimensional digitizer (Patriot, Polhemus): the intersection of the sagittal plane (connecting the nasion and inion) and the coronal plane (linking bilateral preauricular points) defines the standardized positioning of the Cz electrode. This will allow channel positions to be mapped to the Montreal Neurological Institute (MNI) coordinate system, enabling precise spatial normalization across participants. Subsequently, we will measure the head circumference of each participant to select a suitable size head cap equipped with a fNIRS probe. The elastic cap with adjustable sliding mounts allowed dynamic adaptation of source-detector spacing (25–35 mm) based on real-time scalp coupling verification via optical intensity monitoring. This hybrid spatial referencing strategy adapts to changes in scalp curvature and hair density, ensuring optimal light penetration and signal-to-noise ratio.

This system enabled the measurement of oxygenated hemoglobin (HbO) and deoxygenated hemoglobin (HbR) (Ferrari and Quaresima, 2012). The system emits near-infrared light at 670 nm and 850 nm wavelengths with a 10 Hz sampling frequency. Each sensor within the apparatus comprises a light-emitting diode paired with a detector photodiode. In total, the configuration includes 10 light sources and eight detectors, resulting in the formation of 24 channels. As shown in Figure 3. The three-dimensional digital recording of fNIRS channel positions mainly covers six specific brain regions of interest (ROIs) in both hemispheres: primary somatosensory cortex (S1), primary motor cortex (M1), and somatosensory association cortex (SAC). These ROIs focused in this study play an important role in sensory processing and motor execution in the central nervous system (Anders et al., 2004; Bhattacharjee et al., 2020; Sansare et al., 2024). In addition, our previous studies have found that these regions are associated with changes in KOA (Yang et al., 2024).

**FIGURE 3 F3:**
[figure not shown]
**(A)** Near-infrared spectroscopy-statistical parametric mapping toolbox (NIRS-SPM) channel configuration and numbering. **(B)** Schematic representation of fNIRS channel. fNIRS, functional near-infrared spectroscopy.

This study will use the near-infrared spectroscopy-statistical parametric mapping toolbox (NIRS-SPM) implemented in MATLAB to process raw light intensity data obtained from Oxysoft software. The hmrIntensity2OD function is used to convert the data to optical density after eliminating low-quality channels. Head motion artifacts are mitigated using moving standard deviation, spline interpolation, and wavelet artifact correction methods (Guan et al., 2024). The corrected signal is filtered with a bandpass filter to remove physiological noise. The optical density data is transformed into relative changes in HbO and HbR through the modified Beer-Lambert law. Because studies have demonstrated that the HbO concentration possesses a high signal-to-noise ratio, being the most sensitive indicator of local cerebral hemodynamic responses (Gagnon et al., 2012; Ohshima et al., 2023). Moreover, over time, it exhibits higher repeatability and stability (Strangman et al., 2002; Plichta et al., 2006). Therefore, HbO will be chosen as the follow-up analysis in this study. After data preprocessing, we will use the general linear model (GLM) in spectroscopy-statistical parametric mapping (SPM) to model the changes in the concentration of HbO, obtaining the regression coefficient β value for each task condition (Wei et al., 2024). The β value reflects the amplitude of the task-induced blood oxygen signal change and can be used as a quantitative indicator of the neural activation intensity in the corresponding channel region. The design matrix in the model incorporated block-based conditions (boxcar function) corresponding to the three motor tasks, which are convolved with the hemodynamic response function (HRF) to account for the temporal delay inherent in neural activity. Group-level analysis extracts the HbO concentration changes and β values in predefined brain ROIs for subsequent statistics.

### 2.6 sEMG data acquisition and preprocessing

A multi-channel wireless sEMG system (Ultium EMG, Noraxon, United States) will be employed to measure the activity of lower limb muscles during movement. This can reflect muscle activation and functional status. sEMG sensors are placed on the skin surface of target muscles to record the electrical signals generated during muscle contractions. Including a total of seven target muscles of right lower limb as follows: rectus femoris (RF), vastus medialis (VM), vastus lateralis (VL), biceps femoris (BF), tibialis anterior (TA), medial head of gastrocnemius (GM), and lateral head of gastrocnemius (GL). The sEMG sensor is placed at the most prominent part of the muscle belly, ensuring that the sensor positions did not interfere with normal movement. In addition, the sensor is wrapped with a skin membrane to prevent the sensor from loosening or falling during movement.

In this study, Script will be written using Matlab2019b version software to complete the batch processing of surface EMG data. Firstly, the EMG data will be filtered to eliminate various noises in the signal. Then, the DC bias is removed by means of deaveraging, followed by full-wave rectification of the pre-processed signal. The Hilbert transform is used to extract the signal envelope. To reduce individual differences, the Maximum Voluntary Contraction (MVC) will be used to normalize the EMG signals of each muscle (Chowdhury et al., 2013). The indices selected for this study included root mean square (RMS) and median frequency (MF) of frequency-domain features derived from fast Fourier transform.

### 2.7 Clinical scales

In the present study, the Visual Analog Scale (VAS) for pain is employed to assess clinical pain. Specifically, it is a self - reported means for patients to estimate their perception of knee pain on a scale ranging from 0 to 10 (He et al., 2022). KOA symptoms are assessed using the Western Ontario and McMaster Universities Osteoarthritis Index (WOMAC), a specific index for osteoarthritis that ranges from 0 to 96. It is derived from the combined quantitative assessments of knee pain, stiffness, and function (Gandek, 2014). VAS and WOMAC will be assessed before exercise.

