**Methods:**

This study is designed as a cross-sectional observation, aiming to recruit 20 KOA patients and 20 demographically similar healthy controls (HC). Functional near-infrared spectroscopy (fNIRS) is utilized to assess the hemodynamic responses in the cerebral cortex within the specified regions of interest (ROIs), including the primary somatosensory cortex (S1), primary motor cortex (M1), and somatosensory association cortex (SAC). These measurements will be taken during three motor tasks: level walking, ascending stairs, and descending stairs. Simultaneously, surface electromyography (sEMG) is employed to measure muscle activity of the key muscle groups around the knee joint. The VAS and the WOMAC used to evaluate pain and functional symptoms in KOA patients, respectively. Subsequently, the potential correlations between cerebral hemodynamics changes within ROIs and clinical indicators are analyzed.

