**Discussion:**

This study, based on “differential activation of the sensory-motor cortex under movement,” innovatively observes the relationship between pain and functional impairment in KOA patients and activation levels in specific brain regions across different motor environments. This not only provides a basis for early prediction of KOA onset but also offers potential targets for clinical interventions in KOA. Ultimately, the results of this study may open new perspectives for the rehabilitation of chronic musculoskeletal diseases.

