During movement execution, joints are subjected to greater loads and pressures, requiring a higher degree of sensorimotor integration, which may trigger more pronounced pain perception and changes in the activation of related functional brain regions (Marriott et al., 2019; Hutchison et al., 2022; Pan et al., 2024). Investigating these activation changes not only enhances our understanding of the neural mechanisms of pain processing, but also reveal possible impairments in patients’ motor performance. In order to study the activation changes in brain regions under dynamic knee movements, our research group previously employed functional near-infrared spectroscopy (fNIRS) to observe the activation of sensory-motor related brain regions in KOA patients during isokinetic knee movement and ultimately found that these brain regions were in a state of low activation (Yang et al., 2024). Nevertheless, the aforementioned study was limited to observations in specific environments, which differed significantly from the real-life daily activity environment. Bishnoi’s investigation focused on understanding how confronting unexpected challenges during gait—specifically, perturbation walking—affects prefrontal cortical activation in older women diagnosed with osteoarthritis (Bishnoi et al., 2024). The study found that prefrontal cortex activation increased significantly during perturbation walking compared to comfort walking, and this increase was more significant in healthy elderly women. However, the author only observed activation of the prefrontal cortex, and this observation was limited to the treadmill, which was different from daily walking. To clarify the above circumstances, our research group intends to further understand the activation patterns of the sensorimotor cortex of KOA patients in a real walking environment, including level walking and stair walking. Dynamic loading during gait and stair walking, characterized by high volume and frequency, is a fundamental aspect of human daily activities (Andriacchi et al., 2009). Notably, functional mobility limitations are frequently reported as primary challenging aspects of their condition among patients with KOA (Katz et al., 2021).

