This study adopts a cross-sectional research design and utilized fNIRS to investigate brain activities changes in KOA patients under different movement contexts. The specific objective is to analyze the correlation between these changes and the patients’ pain and functional scores. This will provide a more powerful theoretical basis for the central intervention programs for KOA patients.

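### WOMAC is used as the function measure although its 0–96 score includes pain, and the only stated pain rating, taken before exercise, cannot show whether task-evoked pain tracks activation

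*Protocol article*

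**What the plan says.** The Introduction sets the specific objective: to "analyze the correlation between these changes and the patients’ pain and functional scores". Its argument for studying movement is that loading the joint demands more sensorimotor integration, "which may trigger more pronounced pain perception and changes in the activation of related functional brain regions". The abstract's Discussion says the study "observes the relationship between pain and functional impairment in KOA patients and activation levels in specific brain regions across different motor environments".

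The abstract's Methods assigns the scales: "The VAS and the WOMAC used to evaluate pain and functional symptoms in KOA patients, respectively". Section 2.7 then describes them. For pain, "the Visual Analog Scale (VAS) for pain is employed to assess clinical pain", on a 0 to 10 scale. WOMAC is "a specific index for osteoarthritis that ranges from 0 to 96", and "It is derived from the combined quantitative assessments of knee pain, stiffness, and function". On timing, "VAS and WOMAC will be assessed before exercise".

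Section 2.5 produces one β per task condition, so three per patient and region. Section 2.8 relates HbO and β to VAS and WOMAC in KOA patients. It names no WOMAC subscale and no pain score tied to a task.

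**The concern.** There are two separate points.

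**Function.** The score given the functional role contains the construct that VAS is there to measure. If activation follows pain alone, WOMAC will still correlate with activation, and the paper could report a functional correlate that is really a pain correlate. The pain and function halves of the objective would then not be distinct findings.

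**Pain.** The rationale is that movement evokes pain and alters activation. The design collects activation at task level but pain only at baseline. A patient who hurts more on descent than on level walking has the same VAS value against all three βs, so no analysis can ask whether the change in pain goes with the change in activation.

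**Working it through.** The article gives no figure for either point. Its sample size (36, raised to 36/0.9 = 40, so 20 per group) is for a repeated-measures ANOVA and is used here only for n = 20 KOA patients.

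**1. How much pain the WOMAC total carries.** The article gives neither subscale weights nor correlations, so both are assumed and varied. Let the subscales have standard deviations s₁ (pain), s₂ (stiffness) and s₃ (function), with a common correlation c. Then

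r(total, pain) = [s₁ + c(s₂ + s₃)] / √V, where V = Σsᵢ² + 2c(s₁s₂ + s₁s₃ + s₂s₃).

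- Equal weights, c = 0: 1/√3 = 0.58.
- Equal weights, c = 0.7: 2.4/√7.2 = 0.89.
- Weights 20/8/68 (an assumed split adding to 96), c = 0: 20/√5088 = 0.28.
- Weights 20/8/68, c = 0.7: 73.2/√7977.6 = 0.82.

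A function subscale on its own would correlate c with pain. The excess created by using the total is:

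| c (function subscale with pain) | total with pain, 20/8/68 | total with pain, equal weights | excess |
|---|---|---|---|
| 0 | 0.28 | 0.58 | 0.28 to 0.58 |
| 0.3 | 0.54 | 0.73 | 0.24 to 0.43 |
| 0.5 | 0.69 | 0.82 | 0.19 to 0.32 |
| 0.7 | 0.82 | 0.89 | 0.12 to 0.19 |

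Illustration: suppose β correlates 0.5 with pain, function plays no part, and c = 0. The total would still correlate 0.5 × 0.28 = 0.14 to 0.5 × 0.58 = 0.29 with β. The function subscale would correlate 0.

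In the other direction, under 20/8/68 the total correlates 0.95 (c = 0) to 0.98 (c = 0.7) with function. Under equal weights the range is 0.58 to 0.89. If function dominates the score, the two analyses may give similar numbers, and the gain is mainly that the label becomes true.

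**2. Whether regression can separate the scores.** For one correlation at n = 20, 80% power and two-sided 0.05, the detectable |r| is tanh[(1.960 + 0.842)/√17] = 0.59. At 18 patients (36/2) it is 0.62. Bonferroni raises both. There is little room to separate overlapping predictors by adjustment.

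**3. What the pre-exercise VAS can and cannot do.** Each patient has three βs per region and one VAS value.

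- Estimable: the slope of β on baseline pain in each task, and whether slopes differ (a VAS-by-task term).
- Not estimable: the within-patient association between pain in a task and β in that task, because VAS has no within-patient variation.

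**4. An illustrative loss.** Take task pain as the target, with an assumed correlation of 0.5 with β. If baseline VAS relates to β only through task pain, the observed correlation is 0.5 × k, where k is the assumed VAS–task-pain correlation. Fisher z power at n = 20, unadjusted α = 0.05:

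| k | expected r | power |
|---|---|---|
| 1.0 | 0.50 | 62% |
| 0.9 | 0.45 | 52% |
| 0.8 | 0.40 | 42% |
| 0.6 | 0.30 | 25% |

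The result depends on k, which the article does not give. It also ignores Bonferroni: with an assumed family of six ROI tests, power at r = 0.50 is already only about 35%. These figures do not size a defect in the plan.

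**The case against.** The strongest reply is that the plan never undertakes to relate activation to task-evoked pain. Section 2.7 calls VAS a measure of clinical pain, the analysis in section 2.8 is exploratory, the Introduction's sentence is hedged background, and the abstract places activation, not pain, across environments. This stands. A baseline VAS is a coherent measure of clinical pain, and its timing causes no attenuation for that target.

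A reader might infer that no pain link differing by task could be seen. The documents do not support that: with a β for each task, the slopes on baseline VAS can be compared.

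A reader might also infer that pain and function cannot be separated at all. That too goes beyond the text. The limit is in the planned scores, since the function component is part of the instrument being administered.

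It may be said that choosing a subscale belongs in an analysis plan. In part it does, but the article itself assigns WOMAC the functional role and describes only the composite, so its wording needs correcting wherever the detail is settled. A task rating that was never recorded cannot be supplied by any analysis plan.

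Two cautions remain. That VAS is rated only once is inferred from the text, and Figures 1 and 2 are not available here. Repeated pain questions also fall within rest intervals meant for the fNIRS signal to settle, so both groups should be asked in the same way.

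**Conclusion.** The point holds in two limited parts.

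- **WOMAC.** As planned, an activation–WOMAC correlation cannot be read as a function effect, because the score includes pain by construction. The excess overlap with pain is 0.12 to 0.58 in correlation over the assumed weights and subscale correlations. It is small if function dominates the score and pain and function are strongly related.
- **Pain.** The plan can address usual clinical pain, including whether its link with β differs by task. It cannot address whether pain evoked by a task tracks activation in that task, although that mechanism motivates the study. This is a gap against the rationale, not a broken commitment.

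The power and attenuation figures are illustrative only. The group-by-task comparisons of brain and muscle activation are untouched. The point is worth acting on because it bears on the stated specific objective and both remedies are cheap.

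**What to change.** **WOMAC (free).** In sections 2.7 and 2.8, name the WOMAC function subscale as the functional indicator, and report the 0–96 total only as overall symptom burden. Align the abstract. No new item is collected. The subscale may still correlate with pain, but no longer because pain items are in the score.

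**Pain (cheap).** Keep the pre-exercise VAS as the clinical-pain measure. Add the same 0–10 rating after each task, within the 5 min rest already scheduled in section 2.4, using the same procedure in patients and controls. In KOA patients, relate task-specific β to task-specific pain in an exploratory mixed model with a random participant effect. Include task as a fixed effect, so that differences in load between tasks are not read as pain effects. This gives up to 20 × 3 = 60 rating–β pairs, clustered in 20 patients, so they should not be counted as 60 independent observations. The cost is up to 3 tasks × 3 repetitions = 9 short ratings per participant.

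If task ratings are not added, limit the pain conclusions to usual clinical pain.
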